##### Supplementary data (clinical data)

Supplementary data to assess the initial health status and later intervention success include documented clinical data from the initial medical examination (regular orthopedic examination) and patient records which comprise disease duration, medication, basic physiological status (e.g., blood pressure, height, weight, blood lipids) as well as information from the rehabilitation report at discharge (complete details see Table 2).

**Table 2 Tab2:** Supplementary measurements collected from clinical data

Patient record (initial medical examination, physiological status)	Rehabilitation report at discharge (from clinic)
• Anamnesis of the initial orthopedic examination	• Rehabilitation success
• Diagnosis of the initial orthopedic examination	• Degree of disability, level of care
• Duration of the disease and medical history	• Employment status, gradual reintegration
• Therapies to date (medicaments)	• Aftercare recommendation
• Change of medication during rehabilitation	• Benefits for vocational rehabilitation
• Height, weight, waist and hip size	• Ability to work on discharge
• Blood pressure, pulse	• Days of incapacity to work in the last 12 months
• Blood lipids (HDL, LDL, cholesterol, triglycerides)	
• Urine, liver, thyroid gland, blood count values	

In addition, a question directly to the participant about their actual medication “Are you taking any medications, prescribed or otherwise? If yes, please list the name, dose, and frequency” will be collected at T0 and T3.

##### Functional measurements (postural control, motion, and mobility)

Postural control is an important ability and an elementary requirement for the maintenance of balance and stability in static and dynamic processes. One of the most commonly used methods to evaluate postural competency is the quantitative measurement of the center of pressure (CoP). The CoP is the origin of all ground reactionary forces in the transverse plane. The CoP trajectory indirectly allows a quantification of postural competence, based on body sway in a quiet stance on a force plate [53, 54]. It has been shown that portable force plates can be an alternative to conventional force plates [55].

Postural control will be assessed through center of pressure (COP) measures on a balance board system. Therefore, one-legged measurements, two for the left and two for the right leg, and one two-legged, will be performed after one trial with a standing time of 60 s. Mistakes or the inability of standing for that time will be recorded. A sampling rate of 1 kHz and a resolution of 14 bit will be used.

Motion analysis includes measurements of trunk mobility, local dynamic stability of complex trunk movements, and core muscles and lumbar spine coordination.

Trunk mobility is determined by controlled bending of the trunk from an upright standing position. The lumbo-pelvic kinematics in the upright standing position and during forward trunk bending will be measured using two three-dimensional acceleration sensors (Biovision, Wehrheim; size 1 × 1 × 1 cm, 1000 Hz) attached to the skin at the level of thoracic vertebrae 12 (T_12_) and sacral vertebrae 1 (S_1_). The pelvic (Base_pelvic_) and trunk (Base_trunk_) angles in the upright stance will be calculated in the sagittal plane using the orientation of the local coordinate system of the attached sensors in S_1_ and T_12_, with respect to the global coordinate system.

Coordination of the pelvis and lumbar spine is determined by the ratio of lumbar spine rotation to pelvic rotation: lumbo-pelvic ratio (LPR) in the sagittal plane during maximum protrusion. The same test setup is used to measure the LPR as used to determine the range of motion of the trunk.

The range of motion (RoM) of the pelvis and trunk of the patients will be measured in the sagittal plane during a controlled maximum forward trunk bending. The lumbo-pelvic ratio (LPR) will be calculated as the ratio of the changes in lumbar spine orientation to the changes of pelvic orientation. LPR will be calculated for the whole forward bending motion (full) as well as for the first (early), second (middle), and final (late) third of the RoM.

The local dynamic stability of complex trunk movements is quantified by the method of non-linear time series analysis. For this purpose, 30 motion cycles of a three-dimensional trunk movement (kneeling) are used. The local dynamic stability of the trunk during a rhythmic pointing task will be investigated using the short-term Lyapunov exponent (sMLE) as a criterion for the assessment of the neuromuscular control of spine stability. The participants will perform a rhythmic pointing task alternating between the right and left hand in a kneeling position. A total of 30 cycles will be included in the time series analysis. We will measure the motion of the trunk using a three-dimensional (3D) acceleration sensor (Biovision, Wehrheim, Germany; size 1 × 1 × 1 cm, 2000 Hz) attached on the back at the T_2_ (2nd thoracic vertebra) level. The assessment of neuromuscular control will be evaluated using nonlinear time series analysis and reconstructing the state space of the trunk dynamics from the recorded data.

*Mobility tests* comprise the Timed Up and Go Test (TUG) and Chair Rising Test. Before and after the tests, current back pain intensity is recorded using the NRS (Numeric Rating Scale) from 0 to 10.

*Functional measurements* will be performed at all time points (T0/T1 in the rehabilitation center, and T2/T3 in follow-up centers).

### Participant timeline {13}

The main outcome of interest is pain measured as Characteristic Pain Intensity and Disability Score. The trial is divided into three phases: [1] 3 weeks stay in rehabilitation, [2] 9 weeks of supervised aftercare home training (training support by phone and digital media assistance), and [3] 12 weeks of independent aftercare home training. As shown in Fig. 4, measurements will take place at four time points in each group, at baseline (T0), directly before leaving the rehabilitation stay (T1), after 9 weeks of supervised aftercare home training (T2), and after 12 weeks of independent aftercare home training (T3).

### Sample size {14}

For the main study, the sample size calculation was based on a small effect size of *d* = 0.2 as well as assumptions on the normal distribution and variance equality. Alpha-error probability of 5%, beta-error probability of 20%, and a ratio allocation of 1:2 (control vs intervention) were considered. The repeated measures ANOVA for three time points between the groups with a correlation among repeated measures of 0.57 (results from pilot study, unpublished material, based on CPG Disability score) calculate a sample size of 843 (*n* = 562 in the intervention and *n* = 289 in the control group). Assuming a dropout rate of 30%, the total number of participants to be included in the study is *N* = 1204 (power analyses by G*Power; Faul, Erdfelder, Lang & Buchner, 2007) [56].

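### The stated arm sizes do not add up to the stated total, and 843 is not the 80%-power sample size for the stated inputs: on that model it gives about 90%

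*Protocol article*

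**What the plan says.** All the figures are in the protocol article, Sample size {14}. The effect is given as follows: "sample size calculation was based on a small effect size of *d* = 0.2". The error rates and allocation are: "Alpha-error probability of 5%, beta-error probability of 20%, and a ratio allocation of 1:2 (control vs intervention) were considered". The test is described as "The repeated measures ANOVA for three time points between the groups", "with a correlation among repeated measures of 0.57", and the correlation is attributed to pilot data on the CPG Disability score. The section reports that these inputs "calculate a sample size of 843 (*n* = 562 in the intervention and *n* = 289 in the control group"), then allows for 30% dropout and arrives at 1204, using G*Power. The Abstract and Recruitment {15} repeat 1204.

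Statistical methods {20a} plans a repeated measures ANOVA of both co-primary outcomes at T0, T2 and T3, adjusted for center, age and sex. It does not say which term of that model is the confirmatory one. Outcomes {12} names T2 as the main time point.

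**The concern.** Two things fail on a first check. The two arm sizes do not sum to the total printed beside them. The total is also much larger than the stated inputs need, and 562, shown as one arm, is exactly the total that those inputs give for two equal groups.

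The control-arm size and the power are figures that the final report will repeat. A null result would be read against a power of 80%, and that figure does not describe what 843 evaluable patients deliver under any version of the planned analysis examined below.

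**Working it through.** **Inputs (Sample size {14}).** d = 0.2; alpha 0.05; target power 0.80; m = 3 measurements; rho = 0.57; control to intervention 1:2; dropout 30%.

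**1. Sums.**
- 562 + 289 = 851, not 843.
- 843 × 2/3 = 562 and 843 × 1/3 = 281.
- 843 / 0.7 = 1204.3, which matches the target. 851 / 0.7 = 1215.7, which would give 1216.

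So 289 disagrees with the total, the ratio and the target, while 562, 843 and 1204 agree with one another.

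**2. The stated calculation.** For the between-groups test in a repeated measures ANOVA, power comes from a noncentral F with 1 and N − 2 degrees of freedom and

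lambda = N × f² × m / (1 + (m − 1) × rho), where 1 + 2 × 0.57 = 2.14.

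*Equal groups*, f = d/2 = 0.10:
- N = 561: power 0.7994
- N = 562: lambda = 562 × 0.01 × 3 / 2.14 = 7.879, power 0.8001

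The minimum total is 562, and 562 × 1.5 = 843.

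*2:1 groups*, f = 0.2 × sqrt(2/9) = 0.0943, f² = 0.00889:
- N = 632: lambda = 7.875, power 0.8001. In an exact 2:1 split this is 633 = 422 + 211, and 633 / 0.7 gives 905 to recruit.
- N = 843 (562/281): lambda = 10.50, power 0.899
- N = 851 (562/289): power 0.905

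**3. Could another reading give 843 at 80% power?** None of those tried comes within 3%.

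| Variant | Total N |
|---|---|
| Group-by-time interaction, f = 0.10 or 0.0943 | 140 to 157 |
| Two measurements, equal groups | 620 |
| Four measurements, equal groups | 534 |
| Alpha 0.025, equal groups / 2:1 | 682 / 766 |
| One time point, 2:1, two-sided / one-sided | 885 / 696 |
| Baseline-adjusted, r = 0.57, 2:1 | 597 |

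The nearest match is 2:1 allocation at 90% power, about 847, but the document states a beta of 20%.

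**4. What the model assumes about T0.** The between-groups test averages the group difference over its time points, so d = 0.2 has to hold at T0 as well. T0 is clinic admission in a randomised trial, so the expected difference there is zero. Assume instead 0 at T0 and 0.2 at T2 and T3, with 562/281 and compound symmetry.

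- *Group main effect.* The mean difference is (0 + 0.2 + 0.2) / 3 = 0.133, so f = 0.0943 × 2/3 = 0.0629, lambda = 4.67 and power is 0.579.
- *Group-by-time term.* lambda = (562 × 281 / 843) × S / (1 − rho), where S is the sum of squared deviations of the three differences from their mean: 0.0178 + 0.0044 + 0.0044 = 0.0267. This gives 187.33 × 0.0267 / 0.43 = 11.62 on 2 and 1682 degrees of freedom, and power 0.872.

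**5. Sensitivity to rho at 562/281.** The document gives only 0.57; the range is an assumption.

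| rho | Main effect, d = 0.2 at all three times | Main effect, T2 and T3 only | Group-by-time, T2 and T3 only |
|---|---|---|---|
| 0.3 | 96% | 70% | 66% |
| 0.57 | 90% | 58% | 87% |
| 0.7 | 86% | 53% | 96% |

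**The case against.** The strongest reply is that little depends on the error. 289 looks like a slip for 281 and went no further: 1204 follows from 843, and allocation is 2:1 throughout the article. On the stated model the oversizing is conservative, since the trial gets about 90% power where it claims 80%. All of this stands, and it is why the point is a reporting correction and not a challenge to the recruitment target.

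Four stronger readings are tempting, and the document does not support them.

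- *The trial is underpowered at 58%.* That figure holds only for the group effect averaged over T0, T2 and T3. The same analysis also contains a group-by-time term, with about 87% power for the same effects. Statistical methods {20a} does not say which term decides, so neither figure may be quoted without the other.
- *None of the figures can be reproduced.* The target of 1204 follows from 843 and 30% dropout, and 562 is two thirds of 843. What fails is 289 and the step from the inputs to 843.
- *A total was certainly entered as one arm.* The match of 562, and of 562 × 1.5 with 843, is exact and suggests this. The software output is not shown, and the document gives d, not the f that the calculation uses, so it remains an inference.
- *The power is really 91% per endpoint.* That figure belongs to a baseline-adjusted contrast at T2, which is not the planned analysis. It also applies a correlation from the Disability score to pain intensity, for which the document gives none.

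**Conclusion.** The point holds as a correction of stated figures. The control arm is printed 8 too high (289 against 281). The evaluable total of 843 exceeds the roughly 632 that the stated inputs need under 2:1 allocation, and gives about 90% power on the stated model.

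That model rests on a baseline difference that randomisation rules out. With d = 0.2 at T2 and T3 only, 562/281 gives about 58% for the averaged group effect and about 87% for the group-by-time term. The stated 80% matches none of the three.

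These power figures assume 843 evaluable patients, rho = 0.57 at every pair of time points (compound symmetry), alpha 5% for one endpoint, and no gain from the covariates.

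**What to change.** In Sample size {14}:

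1. Keep the target of 1204 and the evaluable total of 843, and replace 289 by 281.
2. Replace the 80% claim with the power that 562/281 gives for the term of the {20a} analysis that decides the trial, and name that term.
3. State the assumed difference at T0, T2 and T3, and show power over a range of rho, for example 0.3 to 0.7 as in the table above.
4. Say that 0.57 comes from the Disability score only, so that its use for pain intensity is visible as an assumption.

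The 91% for a baseline-adjusted T2 contrast may be quoted only if the primary analysis in {20a} is changed to that contrast; otherwise the two sections would disagree in a new way.

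The cost is one rewritten paragraph, plus a decision on which term is confirmatory. Recruitment does not change.

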### Recruitment {15}

The first contact with the staff upon admission to the rehabilitation clinic is either through the corresponding physician (ward or chief physician) or by other medical staff (nurses, therapists, scheduling personnel). The personnel inform patients about the study orally and/or via an information flyer. Study participants receive individual feedback on their health profiles.
Planned/actual: actualDate of first enrollment: 21.09.2020Target sample size: 1204Monocenter/multicenter trial: multicenter trialNational/international: national

## Assignment of interventions: allocation

### Sequence generation {16a}

The method of generating the allocation sequence consists of computer-generated random numbers. A stratified randomization per center is conducted. Concretely, a block randomization with a fixed block size is planned for each center. After assigning a random number (generated by Excel) to a list of numbers (block size), the blocks are sorted by their random number, resulting in a random 2:1 assignment to the intervention or control group for each center at each time point.

### Concealment mechanism {16b}

At the beginning of the study, each center will receive a fixed-size randomization numbers list. Every 2 weeks or when needed, the study therapist will receive the list with additional randomization numbers.

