### Who will take informed consent? {26a}

After admission to the rehabilitation clinic, the patient will be contacted either by the corresponding physician (ward or head physician) or other healthcare workers (nurse, therapist, or scheduler). The first member to contact the patient will inform him/her about the study and hand the flyer with the written information. Furthermore, the physician conducting the initial clinical examination will decide whether the patient is eligible for the study. If eligible, an appointment with the study therapist will be scheduled. The therapist will then explain the details of the study and take the informed consent of the patients who agree to participate.

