One strength of the study is the relatively big sample size and the ability to include patients’ profiles from clinics in six different federation states in Germany. Accordingly, it will be possible to contemplate an external generalizability of the results in Germany. At the same time, the heterogeneity of the study population might limit the internal data interpretation. Sensitivity analyses are planned to consider the effect of covariates. Further, a common limitation of a behavioral intervention including exercises is the impossibility to blind the study staff delivering the intervention and participants to the group allocation; still, the participants are not aware of the study objective. Another limitation is our concealment mechanism: due to constraints of resource management, we are not able to send one randomization number each time, but a few randomization numbers all at once. This could allow a risk of selection bias, because at times, the therapist can predict the next participant group allocation.

The present study provides a feasible individualized program, accessible at home with low costs. One impact of this study is to provide more available rehabilitation aftercare programs to rural populations with different psychosocial risks.

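### The study therapist who takes consent receives coming allocations in advance, from fixed-size blocks in an open trial, so the next arm can be known before consent

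*Protocol article*

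**What the plan says.** The relevant statements are spread over several sections of the protocol article.

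- **Eligibility and consent.** Under Who will take informed consent? {26a}, "the physician conducting the initial clinical examination will decide whether the patient is eligible for the study". An appointment with the study therapist follows: "The therapist will then explain the details of the study and take the informed consent of the patients who agree to participate".
- **Sequence.** Under Sequence generation {16a}, "a block randomization with a fixed block size is planned for each center", at 2:1. The block size itself is not given.
- **Supply of the numbers.** Under Concealment mechanism {16b}, "At the beginning of the study, each center will receive a fixed-size randomization numbers list". After that, "Every 2 weeks or when needed, the study therapist will receive the list with additional randomization numbers".
- **Assignment.** Under Implementation {16c}, staff at the university generate the sequence and the study therapist allocates patients from it.
- **Blinding.** Section {17a} describes an open trial in which participants, instructors and outcome assessors all know the group.
- **Admission of the weakness.** The Discussion says that limited resources prevent sending one number at a time, so a few go out together. It names selection bias as a risk because "at times, the therapist can predict the next participant group allocation".

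**The concern.** Concealment means that whoever enrolls a patient cannot know the arm before the patient is in the trial. Here one person holds the consent conversation, the next few allocations and the act of assignment. The section on the concealment mechanism describes a delivery schedule. It mentions no seal, no release after consent, and no separation between the holder of the list and the person who recruits.

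If the therapist knows the next arm, three things can vary with it: how the study is presented, whether an eligible patient ends up consenting, and on which day consent is taken. The arms may then differ in prognosis for reasons unrelated to treatment. Both co-primary outcomes are self-reported and the planned effect is small (d = 0.2, Sample size {14}), so there is little room for such a difference. The fixed block size adds a second route. In an open trial past allocations are visible, so the end of a block can be deduced even if the list stays out of sight.

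**Working it through.** The plan gives no figure on predictability, so there is none to reproduce. The check has two parts.

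**1. The sections side by side.** The order of events for a patient is: physician confirms eligibility, therapist explains the study, therapist takes consent, therapist allocates ({26a}, {16c}; Trial design {8} also puts allocation after consent). The batch reaches the therapist before these conversations ({16b}). Nothing described stops the therapist from reading the next number between the second and third steps. Foreknowledge from the list reaches to the end of the current batch and no further.

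**2. What fixed blocks reveal without the list.** Inputs: 2:1 ratio and fixed size ({16a}); past allocations visible ({17a}). Assumptions: block size b = 3, 6, 9 or 12, and that the therapist knows or has inferred it.

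Let a block hold I = 2b/3 intervention and C = b/3 control places. The next arm is certain once only one kind of place is left. The expected number of such positions per block is

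I/(C+1) + C/(I+1),

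and dividing by b gives the share of patients whose arm is certain in advance.

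- b = 3: (2/2 + 1/3)/3 = 1.333/3 = 44.4%
- b = 6: (4/3 + 2/5)/6 = 1.733/6 = 28.9%
- b = 9: (6/4 + 3/7)/9 = 1.929/9 = 21.4%
- b = 12: (8/5 + 4/9)/12 = 2.044/12 = 17.0%

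Enumerating every ordering of a block gives the same four shares. It also gives the rate of correct guesses when the therapist always names the arm with more places left: 77.8%, 74.4%, 72.8% and 71.7%. Always naming intervention at 2:1 would be right for 66.7%.

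The gain in overall guessing is therefore modest, 5 to 11 percentage points. The share of certain allocations is not small at any of these sizes. Reading the batch makes every allocation in it certain, so the list is the main route and the fixed blocks the second.

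**The case against.** The strongest reply is that the authors already disclose the weakness, its cause and the risk, and that the physician decides eligibility before the therapist sees the patient. Both points are correct. Disclosure does not remove the risk, however, and no safeguard or analysis is tied to it. The stated cause, that numbers cannot be sent singly, does not explain why a batch must be readable. The physician's decision limits who reaches the therapist, but not how the study is explained or whether and when consent follows.

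A reader might infer more than the article supports:

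- **That the therapist chooses whom to approach.** First contact is by a physician or other clinic staff. A therapist is among those listed, but the text does not say this is the study therapist.
- **That all coming allocations are known.** The Discussion speaks of a few numbers and of occasional predictability.
- **That centers know the block size.** The article does not say so. The shares above are conditional on it.
- **That T0 questionnaires are answered after the arm is known.** The order of questionnaire and allocation is not stated, and the flow charts that might show it are not available here.
- **That a distorted T0 enters the primary model as a covariate.** Statistical methods {20a} adjusts for center, age and sex, and T0 is one of the three repeated outcomes. Baseline pain is a covariate only in the subgroup analysis {20b}.

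These limits stand and narrow the point. They leave the mechanism intact.

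**Conclusion.** The concern holds in this form: within a batch, the person who takes consent can know the next arm beforehand, and fixed blocks in an open trial allow further deduction. The first part rests on the article's own text and admission. The second rests on assumed block sizes and on the size being known or inferred, and gives certainty for about 17% to 44% of patients.

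The size of any bias in the treatment effect cannot be derived from the document. It is tempting to assume a share of selected patients and a gap in prognosis, and to express the product as a fraction of d = 0.2. Neither input has a basis in the article. Because T0 is part of the repeated-measures analysis, a difference already present at T0 would also not pass one-for-one into the group-by-time contrast. Nor does the article support any statement about how an outside quality rating would turn out.

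**What to change.** For all patients still to be enrolled:

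1. Keep sending batches, but as sequentially numbered, sealed opaque envelopes prepared by the university staff who generate the sequence. Each is opened only after consent is signed and the T0 questionnaire is completed. Release through the ProWebDB portal would serve as well if it can do this; the article describes it only for questionnaires and data capture.
2. Generate the remaining sequence with block sizes that vary at random in multiples of 3, and do not disclose them to the centers. This supports the first step and does not replace it.

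The cost is a little preparation for each batch, with no change to treatment, outcomes or sample size. Envelopes meet the stated constraint, since several still travel together.

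Patients already randomized are not corrected, so the limitation in the Discussion stays for them. How many remain depends on the end of recruitment, which the article gives both as 31.12.2021 (with Fig. 4) and as December 2022 (Trial status). Counting from the protocol date of 19.10.2021 and a start on 21.09.2020, the remaining calendar time is 73/466 days = 16%, or 438/831 days = 53% taking 31.12.2022.

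Comparing the effect before and after the change is not worth planning as a check. With even accrual of 1204 at 2:1, no dropout and a simple comparison of post scores, the standard error of the difference between the two periods is √(4.5/n₁ + 4.5/n₂) SD. That is about 0.17 (n = 1015 and 189) or 0.12 (n = 569 and 635), against a planned effect of 0.2, and the comparison is confounded with calendar time.
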